#### Data Analysis

The means (SD) will be calculated for the scale numeric (sum) scores (YMRS, WHOQOL, MHLC, BDKS, DUDIT, DAI-30, AUDIT, relapse frequency/duration) and frequencies will be calculated for categorical variables (gender, age groups, sex, years in illness groups). Parametric tests (analysis of variance, *t* test) will be applied for comparisons between groups. For all statistical tests, *P* values of .05 or lower will be considered statistically significant. Data will be analyzed through the Statistical Package for Social Sciences (SPSS Inc, version 25.00). To test the relationship between two or more variables, logistic and linear regression analyses will be used. The multiple imputation method will be applied to handle missing data.

### Stage 4

Assessment of the applicability of the MoB digital platform will be based on qualitative (users’ feedback) and quantitative (data analysis) testing. The qualitative assessment will be based on the experience of the users with the platform and on the degree to which they were positively affected by its use. Specifically, the focus of the interviews will be on the impact of the platform on their everyday life, as well as on enhancement of ill health self-management skills according to the participants’ responses to the following open-ended questions: (a) “How would you describe your experience with the use of the MoB digital platform?” (b) “What was the impact of use of the MoB digital platform on your life?” and (c) “What was the impact of the MoB digital platform on your ill health self-management skills?” This process will take place via focus groups discussions. Specifically, two focus groups with 8-12 participants each will be recruited including participants who (a) attended the MoB in-person intervention and had used the platform and (b) solely used the MoB digital platform.

The quantitative testing involves anonymous questionnaires provided to users of the MoB digital platform, who will have to answer predefined questions regarding satisfaction parameters relevant to the platform. The first outcome assessed will be the level of users’ satisfaction with the MoB digital platform, measured by the score on a 3-item Likert scale (low, moderate/accepted, high) self-questionnaire exploring users’ perceptions of overall experience; utility, according to their present medical condition and clinical state; practicality on daily usage; improvement of self-management skills; and technical difficulties experienced [51]. The second outcome is the degree of improvement in users’ knowledge as measured by the score on the BDKS [50].

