#### Inclusion and Exclusion Criteria

The following inclusion criteria have been set for participation in the MoB intervention: (1) clinical diagnosis based on the Diagnostic and Statistical Manual of Mental Disorders-5 for BD; (2) aged between 18 and 65 years; (3) signed the informed consent form; (4) stable mood status at the beginning of the MoB in-person intervention based on clinical assessment, conducted by the principal investigator (AH); (5) experience of the illness for at least 1 year based on the medical record; (6) adequate awareness of the illness, based on the following guide: (a) are you aware of the reason(s) you are using mental health services/under medication? and (b) are you aware of the aim of the educational intervention in which you may participate?; and (7) familiarity with computer use.

The exclusion criteria are: (1) intellectual disability (IQ<70), based on the Wechsler Adult Intelligence Scale [42]; (2) brain damage (eg, following a stroke) based on diagnostic tests; (3) acute phase of the illness, based on clinical assessment and use of the Young Mania Rating Scale (YMRS; total score <12) [43] and/or Beck Depression Inventory (total score <17) [44]; and (4) substance use problems at the beginning of this stage according to the Alcohol Use Disorders Identification Test (AUDIT; total score <9) [45] and Drug Use Disorders Identification Test (DUDIT; total score <2 for women or <6 for men) [46].

All eligible participants will be randomly assigned (in terms of gender, age, duration of illness) into the intervention group and the control (waiting) group. With the aim of obtaining a moderate correlation effect, with 80% statistical power and .05 level of statistical significance, 40 participants are needed in the intervention group and 40 participants are needed in the control (waiting) group.

The criteria for discontinuing participation in the intervention group are disorder relapse and nonadherence to pharmacotherapy (discontinuation of medication).

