#### Intervention Procedure

The form of this intervention will be in groups or in person according to the participant’s choice (similar to the data collection process as detailed above). Additionally, all participants of this group will have access to the MoB digital platform and will be assessed via a checklist on the frequency and extent to which they use the digital platform in each in-person session.

The implementation methodology of the MoB in-person intervention will include videos and PowerPoint presentations, as well as interactive learning methods such as role playing, empowerment exercises, and live discussions.

The MoB in-person intervention will comprise a total of 12 educational sessions. Each session will have a duration of 1.5 hours and the maximum number of participants in the groups will be 12 patients. At the beginning of each session, the participants will be given the opportunity to record their feedback for the previous session and the impact of the training intervention so far for themselves and for their families/significant others. The intervention will be performed at Cyprus University of Technology and will be implemented by the principal investigator (AH). Participation in the educational intervention is free of charge. Moreover, there is no financial benefit for those participating in the study (participants, researchers) in terms of reimbursement or any other material benefit.

Those who wish to withdraw participation prior to completion of the intervention will be able to continue to receive information/knowledge about their illness through the digital platform.

The control (waiting) group will only have access to the MoB digital platform. Yet, it should be noted that the control (waiting) group will also receive the MoB in-person intervention if its effectiveness is shown at the end of the study. In this way, all participants will be given the chance to receive the MoB intervention.

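### The stated between-group tests name no baseline adjustment and make no allowance for session groups in the intervention arm, which costs power and understates the standard error for group-taught participants

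*Protocol article*

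**What the plan says.** Data Analysis (Stage 3) lists parametric tests, namely analysis of variance and the t test, for the arm comparison: "test) will be applied for comparisons between groups". Regression appears separately and is not tied to that comparison: "To test the relationship between two or more variables, logistic and linear regression analyses will be used".

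Other sections describe features of the design that bear on this choice:

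- **Assignment.** Inclusion and Exclusion Criteria: participants are "randomly assigned (in terms of gender, age, duration of illness").
- **Sample size.** Same section: the target is set "With the aim of obtaining a moderate correlation effect, with 80% statistical power and .05 level of statistical significance". The resulting size is given as 40 per arm.
- **Delivery.** Intervention Procedure: "The form of this intervention will be in groups or in person", as each participant chooses, and "the maximum number of participants in the groups will be 12 patients". Controls have the digital platform only.
- **Timing.** Effectiveness Evaluation: four assessments in both arms. The first precedes the in-person sessions; the others come at their end and 6 and 12 months later. The null hypothesis is that both arms improve equally.
- **Illness duration.** Discussion, Projected Findings and Significance: care will be taken to control this confounder in the analysis. No method is given.

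**The concern.** The tests named do not use what the design supplies, for two reasons.

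**Precision.** Each scale has a pre-intervention value in both arms, and the assignment takes account of three prognostic factors. Adjusting for these costs nothing in data collection. In a trial of 80, in a country where the authors call recruitment a challenge, the lost precision matters.

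**Validity of the standard error.** Participants who choose group teaching share 12 sessions of role play and live discussion with the same peers, so their outcomes may be correlated. Controls have no such groups. This is a partially nested design. A t test or ANOVA that treats all 80 as independent gives too small a standard error whenever the within-group correlation is positive. The error runs towards declaring the intervention effective, and offering the in-person course to controls depends on that declaration.

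**Working it through.** **Inputs from the article:** 40 per arm, 80% power, alpha 0.05, a moderate correlation effect, groups of at most 12.

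**Assumptions (not in the article):** a two-sided test; r = 0.3 as the moderate correlation; baseline-to-follow-up correlation rho = 0.3, 0.5 or 0.7; intraclass correlation (ICC) 0.02 to 0.10; group size m = 10 or 12; half or all of the intervention arm group-taught.

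**1. Reproducing 40 per arm.**
d = 2r/√(1 − r²) = 0.6/√0.91 = 0.629.
n = 2(1.96 + 0.842)²/0.629² = 39.7, so 40 per arm.
Power at 40 per arm is 80.3% by the normal approximation and 79.3% by the exact t test. The stated size therefore matches an unadjusted comparison of independent observations.

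**2. Baseline adjustment.** ANCOVA multiplies the residual SD by √(1 − rho²). A change score multiplies the SD by √(2(1 − rho)). Exact power at d = 0.629 and 40 per arm:

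| rho | post-score t test | change-score t test | ANCOVA (effective d) |
|---|---|---|---|
| 0.3 | 79% | 65% | 83% (0.629/0.954 = 0.659) |
| 0.5 | 79% | 79% | 89% (0.629/0.866 = 0.726) |
| 0.7 | 79% | 95% | 97% (0.629/0.714 = 0.881) |

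A change score gains nothing over the post score at rho = 0.5, loses power below that, and never beats ANCOVA.

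**3. Session groups.** With a share s of the intervention arm in groups of m, the design effect for the grouped part is DE = 1 + (m − 1)ICC. The true variance of the arm difference, relative to what the t test uses, is V = [s·DE + (1 − s) + 1]/2. The true error rate at nominal 5% is 2[1 − Φ(1.96/√V)].

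Example: s = 1, m = 12, ICC = 0.10. DE = 1 + 11 × 0.10 = 2.10; V = (2.10 + 1)/2 = 1.55; √V = 1.245; 1.96/1.245 = 1.574; error rate 11.5%.

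| ICC | all grouped, m = 10 / 12 | half grouped, m = 10 / 12 |
|---|---|---|
| 0.02 | 6.0% / 6.3% | 5.5% / 5.6% |
| 0.05 | 7.7% / 8.3% | 6.3% / 6.6% |
| 0.10 | 10.4% / 11.5% | 7.7% / 8.3% |

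Simulation of the plain t test (40,000 runs per scenario) agrees. With four groups of 10 it gives 7.3% at ICC 0.05 and 10.6% at ICC 0.10. With half the arm in two groups of 10 it gives 6.4% and 7.6%. At ICC 0.01 the inflation is negligible (5.6% with four groups of 10).

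**4. Both together.** With all in groups of 10 and ICC 0.05, the correct standard error without baseline adjustment gives 72% power. Adding the baseline covariate gives about 84% at rho = 0.5. These are normal-approximation figures and leave out the degrees-of-freedom cost of having few groups.

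**The case against.** Several stronger readings are tempting, and the article does not support them.

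- **That the plan ignores the balancing factors.** The Discussion promises control of illness duration, one of the three. What stands is that Data Analysis gives no method for it and that adjustment for gender and age is not mentioned.
- **That the plan discards baseline.** Effectiveness is framed as improvement, so change-score t tests or repeated-measures ANOVA are fair readings. What stands is that no baseline covariate is named, that neither reading is more efficient than ANCOVA, and that neither handles session groups.
- **That the trial has only about 60% power.** That needs d = 0.5, which is not the article's effect; the stated size matches d = 0.63.
- **That error inflation of up to 11.5% is to be expected.** That needs the whole arm in groups of 12 and an ICC of 0.10. Format is by choice, 7 of the 13 Stage 1 participants had personal interviews, and some were reluctant to join focus groups because of stigma. One person delivers all sessions, so differences between facilitators add nothing to the ICC.
- **That comparing group with individual teaching would lack a randomised counterpart.** True in principle, but no such comparison is planned.

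It may also be said that an article leaves the exact model to the full protocol or analysis plan. That covers the form of ANOVA. It covers less well a stated choice of test that treats observations as independent, in a design with grouped delivery in one arm.

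**Conclusion.** The concern holds in a limited form. The tests named for the arm comparison include no baseline covariate, the promised control of illness duration has no counterpart in Data Analysis, and correlation within session groups is not addressed.

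Baseline adjustment would raise power from about 79% to 83-97%, given d = 0.63 (inferred from the stated sample size) and an assumed rho of 0.3-0.7. Ignoring session groups puts the true error rate at about 6-11.5% if all intervention participants are group-taught and 5.5-8.3% if half are, for an assumed ICC of 0.02-0.10 and groups of 10-12. The inflation vanishes as the ICC or the share taught in groups goes to zero. The direction of both effects is certain for positive rho and ICC; their size is not, because the article gives neither value nor the share choosing groups. The plan should be changed, but the trial is not undermined.

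**What to change.** For each scale, compare arms with baseline score, gender, age and duration of illness as covariates, keeping the last two continuous. This also reconciles Data Analysis with the Discussion.

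Use a repeated-measures mixed model over the three post-baseline assessments, with:

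- arm, time and their interaction;
- a participant random effect or an unstructured within-person covariance;
- a separate session-group random effect only for group-taught intervention participants, set to zero for controls and the individually taught;
- Satterthwaite or Kenward-Roger degrees of freedom.

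The participant-level term must not be left out. Without it, coding controls as groups of one lets the group effect absorb person-to-person variance and imposes it on the few real groups, which inflates the standard error and destroys power. A simpler alternative is to fit the same covariates and session-group effect separately at each time point.

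Record a session-group identifier for each participant, and recheck 40 per arm under a stated rho and ICC.

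The cost is revised analysis wording and one extra variable. The drawback is that, with about four groups or fewer (40 participants in groups of 10-12), the group variance is poorly estimated and confidence intervals for the arm effect widen.

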#### Effectiveness Evaluation

Evaluation of the effectiveness of the MoB in-person intervention will be based on the degree of improvement in the following outcome variables defined according to the findings of the literature review completed in Stage 1: (1) self-perceived quality of life level, as measured by the World Health Organization Quality of Life Assessment (WHOQOL) tool [47]; (2) self-perceived health-related locus of control, as measured by the Multidimensional Health Locus of Control (MHLC) scale [48]; (3) ability to control impulses, as reflected in one’s sexual and aggressive behavior, measured by the items “aggressive behavior” and “sexual interest” of the YMRS [43]; (4) substance use problems, measured by the AUDIT (alcohol use) [45] and DUDIT (drug use) [46] tools; (5) adherence to pharmacotherapy, measured by the Drug Attitude Inventory (DAI-30) tool [49]; (6) frequency of relapses assessed by the reduction of the number and duration of hospitalizations for the 2 years following the end of the educational intervention; and (7) BD knowledge level assessed by the Bipolar Disorder Knowledge Scale (BDKS) [50].

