
There will be four evaluation time points. The first evaluation time point will be prior to implementation of the MoB in-person intervention, the second will take place immediately after completion of the MoB in-person intervention, and the third and fourth evaluations will be applied at 6 and 12 months, respectively, after completion of the MoB in-person intervention. These time points have been determined according to the systematic review completed in Stage 1 [14].

The control group will be assessed via the same evaluation tools as the intervention group, and at the same time periods. This will test the null hypothesis that patients who solely receive pharmacotherapy demonstrate the same improvement as the intervention group.

The educational meetings will be held at Cyprus University of Technology in a room specially designed for this purpose that is soundproof, without windows, and chairs placed in a circular arrangement to allow for eye contact, along with small tables on either side to keep notes.

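### Effectiveness rests on seven unranked outcome variables (11 scores), each test judged at an unadjusted .05, with no rule for which result shows effectiveness

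*Protocol article*

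**What the plan says.** All references are to the protocol article, Methods, Stage 3.

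- **Basis of the claim.** Under Effectiveness Evaluation: "Evaluation of the effectiveness of the MoB in-person intervention will be based on the degree of improvement in the following outcome variables". Seven numbered variables follow: quality of life, health locus of control, impulse control, substance use, adherence, relapse and knowledge. None is called primary.
- **Times.** "There will be four evaluation time points", in the same section: one before the sessions, one straight after them, and two at 6 and 12 months after completion. Hospitalization is the exception. Its number and duration are defined over the 2 years after the intervention ends.
- **Tests.** Under Data Analysis: "Parametric tests (analysis of variance, *t* test) will be applied for comparisons between groups". In the same paragraph, for all tests, P "values of .05 or lower will be considered statistically significant".
- **Action.** Under Intervention Procedure, controls are to receive the sessions "if its effectiveness is shown at the end of the study".
- **Sample size.** Inclusion and Exclusion Criteria gives the basis as "With the aim of obtaining a moderate correlation effect, with 80% statistical power and .05 level of statistical significance". The resulting requirement is 40 per group. No outcome or time point is attached to this.

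**The concern.** A .05 threshold limits the false-positive rate to 5% for one test. Here the effectiveness claim rests on a list of outcomes with no order among them, and the same .05 applies to every test made on that list. The chance that something on the list reaches significance with no true effect is then well above 5%, and nothing in the text says how a mixed set of results would be read.

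Two things depend on this. One is the decision to offer the sessions to the waiting group. The other is the article's Conclusion, which looks forward to robust evidence that would support taking the intervention into mental health services.

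**Working it through.** **1. The plan's own figure.** The effect is described only as a moderate correlation. Assume r = 0.30.

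- d = 2r/√(1−r²) = 0.60/√0.91 = 0.629.
- n per group = 2(1.960 + 0.842)²/0.629² ≈ 39.7, so 40. Normal-approximation power at 40 per group is 80.3% (exact t test 79.3%).

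The stated 40 is therefore reproduced for **one** two-sided comparison at .05. Other readings tried do not give it: d = 0.5 needs 63 per group, and a Fisher z test of r = 0.30 needs 85 in total two-sided or 68 one-sided.

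**2. Count of scores.** From Effectiveness Evaluation and Data Analysis: WHOQOL 1, BDKS 1, YMRS 1, DAI-30 1, DUDIT 1, AUDIT 1, MHLC 3 subscales, number of hospitalizations 1, days of hospitalization 1. Total 11.

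**3. Count of tests.**

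- One test per score, for example one ANOVA per score: 11.
- Separate tests at each post-baseline visit (an assumption, not stated in the protocol): 9 scores × 3 visits + 2 hospitalization outcomes = 29.

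**4. Chance of at least one P≤.05 with no true effect.** For k independent tests this is 1 − 0.95^k for any significant result and 1 − 0.975^k for one favouring the intervention (two-sided testing assumed; sidedness is not stated).

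- k = 11: 1 − 0.95^11 = 43.1%; 1 − 0.975^11 = 24.3%.
- k = 29: 1 − 0.95^29 = 77.4%; 1 − 0.975^29 = 52.0%.

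Positive correlation lowers these. The documents give no correlations, so a multivariate normal simulation (100,000 draws) was run over an assumed range:

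| Tests | Correlation between outcomes | Correlation between visits | Any P≤.05 | Favouring intervention |
|---|---|---|---|---|
| 11 | 0.3 | – | 37.6% | 19.1% |
| 11 | 0.5 | – | 30.4% | 15.2% |
| 29 | 0 | 0.3 | 75.6% | 49.7% |
| 29 | 0.3 | 0.5 | 67.0% | 36.7% |
| 29 | 0.5 | 0.8 | 48.7% | 25.0% |

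The last column treats one direction of each MHLC subscale as favourable, although the article calls neither direction better. Without those three subscales, 8 independent tests give 1 − 0.975^8 = 18.3%.

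At the lowest values for one test per score, the inflation is still about sixfold: 30.4/5 = 6.1 and 15.2/2.5 = 6.1.

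**5. Can the sample size absorb a correction across all scores?** Bonferroni over 11 tests uses .05/11 = .0045. With d = 0.629 that needs 69 per group, and 40 per group gives 49% power. The planned size supports one confirmatory test, not 11.

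**The case against.** The strongest reply is that this is a journal article. Outcome hierarchy, multiplicity handling and the definition of success are commonly left to a full protocol or analysis plan, and neither is shown. A per-test threshold does not in itself exclude a hierarchy defined elsewhere. That would answer a complaint about silence. It does not answer this one fully, because the article fixes .05 for every test and makes an unranked list the basis of the effectiveness claim. A later document that set an adjusted threshold would contradict that sentence.

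Other parts of the reply stand and limit the point:

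- A reader might infer that every score is tested separately at every visit. The article gives measurement times and names ANOVA as well as t tests, so one test per score fits the text equally well.
- A reader might count 11 × 3 = 33 tests. The two hospitalization outcomes have a 2-year window, so 29 is the most that per-visit testing supports.
- A reader might infer that one significant result is enough to declare effectiveness. The article never says so; it leaves the rule undefined.
- Any preference for one primary outcome is partly a matter of choice. The null hypothesis in the Introduction names relapse rate as well as quality of life.

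**Conclusion.** The point holds in this form: no ranked outcome, an unadjusted .05 for all tests, and an action that depends on effectiveness being shown with no rule for showing it. With no true effect, at least one P≤.05 has a chance of about 30–43% with one test per score, or about 49–77% if visits are tested separately. For results favouring the intervention the figures are about 15–24% and 25–52%, against a nominal 2.5%. These rest on two-sided tests and on assumed correlations of 0 to 0.5 between outcomes. The per-visit figures also rest on an unstated testing scheme, with correlation between visits from none up to 0.8.

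It is tempting to conclude that a chance finding of effectiveness is more likely than not. The documents do not support that. With one test per score, even the chance of any significant result stays at or below 43%. Effectiveness also means a favourable result, and with 29 tests that chance passes 50% only when the tests are independent or nearly so.

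**What to change.** Replace the .05-for-all sentence in Data Analysis as follows.

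- Before outcome data are examined, the investigators name one primary outcome at one time point, tested at .05. WHOQOL total at 12 months is one candidate. Relapse is another, since the Introduction's null hypothesis names it too. Tie the sample-size statement to the outcome chosen.
- In Intervention Procedure, define effectiveness being shown as that primary test favouring the intervention.
- Test each of the other ten scores once, with Holm adjustment (smallest P against .05/10 = .005). Keep hospitalization on its stated 2-year window.
- Report the other visits as estimates with confidence intervals.

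This keeps the primary claim at 5% and leaves 40 per group matched to a single comparison, on the r = 0.30 reading. No visit, instrument or participant is added. The cost is an amendment in wording and fewer secondary results that can be called significant. Recruitment began in the first half of 2021, so the amendment should be dated and should record that outcome data had not been examined.

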#### Data Collection and Analysis

The form of the data collection interview, focus group or personal interview, was designed to be assigned according to the participant’s convenience. Since Cyprus is a small island with approximately 1 million citizens, some of the participants were reluctant to participate in focus group discussions due to the social stigma of mental illness [40]. Participation in personal interviews was expected to preserve their anonymity.

A semistructured guide with open-ended questions, set up by the research team according to relevant literature, was used for data collection in this stage. The interview guide included the following questions:

Please tell us what you know about your mental health condition/BD.Please describe what you would like to know about bipolar disorders.Please describe in what way and on what topics you would like to be educated and increase your knowledge on bipolar disorders?Please describe your expectations from an educational intervention regarding its impact on your everyday living.Would you like this intervention to be implemented one-on-one or in a group?How long would you like the intervention to last?What is your level of engagement with the internet?Are you familiar with computer use?

The original intention was to have two focus groups (6-10 people per group); however, in the process of the research, only one focus group was ultimately deemed to be necessary. The focus group participants met two to three times. In the second meeting, the themes revealed in the first meeting were verified and enriched where possible. During the third meeting, the researchers interpreted the data, followed by a discussion with the participants. This method was also applied to personal interviews (2-3 meetings with each participant). Data analysis was based on the conventional mode of content analysis [41].

### Stage 2

The purpose of the development of the ΜoΒ in-person intervention is to create an applicable, feasible, and effective intervention to enhance BD knowledge and ill-health self-management skills in people diagnosed with BD. Specifically, a textbook has been devised explaining in detail the step-by-step process and the techniques of the experimental educational method of the MoB in-person intervention.

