
#### Empirical Qualitative Exploration of Educational Needs

Regarding the qualitative exploration of the educational needs of ill-health self-management skills in people diagnosed with BD, a total of 13 participants were interviewed (8 women, 5 men). Specifically, since participation in interviews was designed to include both personal and focus group modes, we completed one focus group with 6 participants and 7 personal interviews (May to September 2020). The simultaneous data collection and analysis of emerged themes allowed us to determine thematic saturation up to this sample size. Thus, we did not proceed to an additional focus group as intended. Moreover, the fact that the participants came from different educational, social, and professional backgrounds supported the criterion of data saturation. By April 2021, all three meetings had been completed with all 13 participants. Relevant data defined the design of the MoB intervention and are expected to be published by the end of 2021.

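### The Stage 4 qualitative assessment of the platform offers focus groups only, although the protocol itself reports that stigma keeps some patients out of focus groups (cheap improvement, minor)

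*Protocol article*

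**What the plan says.** Methods, Stage 4 of the protocol article sets three open-ended questions: the experience of using the platform, its impact on the user's life, and its impact on self-management skills. The text first speaks of interviews, but then fixes the format: "This process will take place via focus groups discussions". It adds that "two focus groups with 8-12 participants each will be recruited", drawn from (a) people who attended the in-person sessions and used the platform and (b) people who used the platform alone. No individual option is stated.

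The earlier stages are arranged differently:

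- **Stage 1, Data Collection and Analysis.** Focus group or personal interview followed the participant's convenience. The reason given is that on a small island "some of the participants were reluctant to participate in focus group discussions due to the social stigma of mental illness". Of the alternative it says: "Participation in personal interviews was expected to preserve their anonymity".
- **Results, Stage 1.** "we completed one focus group with 6 participants and 7 personal interviews".
- **Stage 3, Intervention Procedure.** "The form of this intervention will be in groups or in person according to the participant’s choice". The Stage 1 results also list having both personal and group options among the participants' own suggestions for the intervention.

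The Stage 4 quantitative part, described directly afterwards, uses anonymous questionnaires for platform users.

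**The concern.** The protocol identifies a barrier to group participation, answers it in Stage 1 with an individual option and keeps that option in Stage 3. It then omits it from Stage 4 without giving a reason. Someone who took the Stage 3 sessions individually so as not to be seen by other patients would have to sit with 7 to 11 others to give open-ended feedback.

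This matters because of who the platform may suit. The Introduction says web-based education may be more favourable for people who meet stigma, and the literature review says such formats attracted them. Part of the platform's rationale thus concerns a subgroup that a group-only format is likely to under-represent. Under Design, the Stage 4 findings are to be used to enrich the platform further, so selective participation could influence its development. The Limitations section mentions only age range and language, so a reader is not warned.

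**Working it through.** **Inputs.** Stage 1 split: 6 in a focus group and 7 in personal interviews (Results, Stage 1). Stage 4: two groups of 8-12 (Methods, Stage 4). Planned Stage 1 format: two focus groups of 6-10 (Stage 1, Data Collection and Analysis). Trial size: 40 + 40 = 80 (Stage 3).

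**Reproducing the plan's figure.** 6 + 7 = 13, and 8 women + 5 men = 13. Both agree with the stated total.

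**Share interviewed individually.** 7/13 = 0.538, or 54%. The exact (Clopper-Pearson) 95% interval is 0.251 to 0.808. More than half is correct, but by one person.

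**What that share does not measure.** Format followed convenience, and only an unspecified some were reluctant because of stigma, so the number who chose an interview for that reason lies somewhere between some and 7. The split also depends on when data collection stopped. A second focus group was intended but not held, because saturation had been reached. Had it added 6-10 new people with the seven interviews unchanged (assumption), the share would have been 7/(13 + 6) = 7/19 = 37% down to 7/(13 + 10) = 7/23 = 30%. The individual route would still have been a substantial one, but the confidence interval does not capture this dependence.

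**Stage 4 qualitative sample.** 2 × 8 = 16 to 2 × 12 = 24 people, all seen in groups.

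**Formats side by side.**

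| Stage | Purpose | Individual format offered? |
|---|---|---|
| 1 | Educational needs | Yes, by convenience |
| 3 | In-person sessions | Yes, by choice |
| 4, qualitative | Platform experience and impact | Not stated; focus groups only |
| 4, quantitative | Satisfaction and knowledge | Anonymous questionnaire |

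**How far the questionnaire fills the gap.** It covers overall experience, utility, daily practicality, improvement of self-management skills and technical difficulties, plus the knowledge scale. That overlaps with two of the three open-ended topics, experience and self-management skills. Its satisfaction items are predefined and answered on a three-level scale, so it cannot supply the free accounts, least of all on life impact.

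**The case against.** The strongest reply is that nobody is excluded from the evaluation. The anonymous questionnaires stay open to platform users, platform use is recorded by checklist at each in-person session, and web analytics cover visitors. This stands. A reader might infer that stigma-sensitive patients drop out of the platform's evaluation altogether, and the documents do not support that. What remains is likely under-representation in the qualitative component.

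A reader might also multiply 7/13 by 80 and conclude that about 43 trial participants would have no route into Stage 4. That does not follow: Stage 4 recruits 16-24 people and never planned to interview all 80, and 7/13 is not a rate of refusing groups. Nor do the documents make stigma-sensitive patients the main target users. The platform is described as serving people with bipolar disorder generally, its informative part is open to anyone interested, and the literature review names younger participants too as attracted to web formats.

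It can further be said that focus groups are a legitimate way to gather feedback on a shared platform, that qualitative samples need not be proportionally representative, and that a journal article may leave fallback arrangements to a fuller document. The first two are true but do not explain why a barrier that the protocol itself reports is ignored here. On the third, the article does not stay silent on format: it fixes one. Pseudonyms, promised under Ethics and Data Management, do not hide a person from others in the same room.

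Finally, the Stage 3 section gives no stigma reason of its own for offering a choice; it refers back to the data collection process. That link is therefore indirect.

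**Conclusion.** The point holds in a limited form. Stage 4 fixes a group-only format for the open-ended assessment, against the protocol's own evidence that some patients avoid groups because of stigma and against its practice in Stages 1 and 3. Users who avoid groups are likely to be under-represented among the 16-24 people interviewed.

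The extent of this cannot be calculated from the document. The 54% seen individually in Stage 1 shows only that the individual route was well used. The conclusion assumes that reluctance in Stage 4 resembles that reported in Stage 1. It is a risk of selection, not a demonstrated loss.

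The stakes are low. The Stage 3 comparison, its outcomes and its sample size are untouched. This is a cheap improvement of minor weight.

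**What to change.** In Methods, Stage 4, replace the focus-group-only rule with the Stage 1 rule: focus group or personal interview, according to the participant's convenience. Keep the three open-ended questions unchanged, and offer both formats within (a) session attenders who used the platform and (b) platform-only users. If the group-only format is kept, state the selection risk under Limitations.

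The cost is some extra interviewing time for the same researchers and less group interaction in the data. No new interview guide is needed.
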